### Intervention

Following baseline measures, the intervention group will receive an introduction to the downloading process and a demonstration of the app [28,36-39]. They will also be provided with a user’s manual and 2 resistance bands with a resistance of their choice (TheraBand, The Hygenic Corporation), one of which is for backup. The intervention group will perform a 6-week home-based exercise program delivered by the ParaGym mobile exercise app, comprising three 35-minute exercise sessions per week. The app offers a different workout every day, and participants get to choose the days on which they want to exercise. An exercise session consists of 4 parts: warm-up, 2 exercise parts, and cooldown. The first exercise part focuses on the correct execution of the exercises at a moderate intensity and prepares the musculature for the high-intensity second part. Exercise sessions aim at various training goals, such as stabilization of the shoulder girdle and improvement of wheelchair mobility. The waitlist control group will only maintain usual care and receive access to the mobile app after postintervention measurements.

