### Measures

#### Primary Outcomes

##### Overview

The primary outcomes are feasibility, usability, and safety. Six weeks after commencing the intervention, semistructured interviews will be conducted via phone to investigate feasibility and usability. An interview guide was conceptualized based on interview domains and topics in similar studies [27,36,39-43]. The following topics will be addressed: (1) overall experience, (2) ease of use, (3) app functionality, (4) perceived safety, (5) technical functionality, (6) communication, (7) perceived effects and usefulness, (8) adherence and motivation, and (9) recommendation. The interviews will be audio recorded with the consent of the participants.

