##### Feasibility

During their first site visit, participants in both the intervention and waitlist control groups will be provided with an exercise diary (Multimedia Appendix 2). They will be asked to record the following: (1) any physical activities, including app exercise sessions, additional exercise sessions (eg, hand biking), and physical therapy; (2) the time spent performing the exercise; (3) the intensity of the exercise; and (4) any annotations concerning the exercise sessions as needed (eg, whether the session adapted by the algorithm was appropriate in terms of the choice of exercise and intensity). This will help obtain more information about the feasibility of the app in addition to the information provided in the retrospective interviews and help assess adherence to the program. Adherence rates in terms of completed sessions will also be measured based on app use data. Furthermore, retention rates will be measured by assessing dropout rates and reasons. As both adherence and retention are study outcomes, they should not be influenced by the investigators. Therefore, no measures will be taken to promote either of them. All outcome measures will be obtained regardless of adherence.

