##### Safety

The safety of the app-based exercise program will be determined based on the occurrence of intervention-related AEs and SAEs. Participants will be instructed to report any AEs or health-related interruption of the intervention within 24 hours. AEs and SAEs will be classified by the grade of severity based on the Spinal Adverse Events Severity System version 2 (SAVES-V2) scale [48] (Table 2) and expectance. The following AEs and SAEs can occur because of physical strain or are common complications after SCI and are, therefore, classified as expected AEs or SAEs: (1) autonomic dysreflexia, (2) pressure ulcers, and (3) shoulder pain [49].

**Table 2 table2:** Classification of adverse events (AEs) and serious adverse events (SAEs) based on the Spinal Adverse Events Severity System version 2 scale.

Severity of AE or SAE	Clinical impact
1	AE—no treatment
2	AE—outpatient treatment
3	SAE—inpatient treatment
4	SAE—life-threatening injury
5	SAE—death

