#### Quantitative Analysis

Quantitative data analysis will be performed using SPSS. All data will be tested for normal distribution using the Shapiro-Wilk test. Study participant characteristics will be presented descriptively by calculating means and SDs for normally distributed variables. Median values and IQR will be calculated for skewed continuous variables, and absolute and relative frequencies will be calculated for nominal variables. Group differences at baseline will be calculated for independent samples using a 2-tailed *t* test, Mann-Whitney *U* test, or chi-square test depending on the distribution and level of measurement. At t_1_, normally distributed continuous variables will be analyzed using a mixed analysis of variance model to test for significant effects for group and time. For skewed continuous variables, Wilcoxon and Mann-Whitney *U* tests will be conducted to test the differences between the groups and between t_0_ and t_1_. The significance level will be set at *P*<.05. Absolute and relative frequencies will be reported for adherence and retention.

Feasibility will be assumed if (1) at least 66% of the training sessions (equivalent to 2 out of 3 sessions per week) are completed [43] and (2) the retention rate is at least 75% [67]. Exercise diaries will be analyzed in terms of the frequency, duration, and intensity of the training sessions. Safety will be assessed by comparing the number of study-related AEs or SAEs in the intervention group with that in the waitlist control group [68].

Spearman correlations will be used to assess the association between performance and strength outcomes and SCIM III and SF-36 outcomes. Subgroup analyses might be conducted for lesion level (high vs low paraplegia) and age. Missing data will not be imputed.

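### The between-group safety comparison counts only study-related adverse events, so the waitlist group cannot supply the background rate that the comparison needs

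*Protocol article*

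**What the plan says.** All references are to the protocol article.

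- **Status of the outcome** (Primary Outcomes, Overview): "The primary outcomes are feasibility, usability, and safety".
- **Definition** (Safety): "The safety of the app-based exercise program will be determined based on the occurrence of intervention-related AEs and SAEs". No comparator is named. Events are graded for severity on a five-level scale and classed as expected or not.
- **Analysis** (Quantitative Analysis): "Safety will be assessed by comparing the number of study-related AEs or SAEs in the intervention group with that in the waitlist control group". No test, threshold or denominator is attached to this sentence.
- **Control condition** (Intervention): "The waitlist control group will only maintain usual care and receive access to the mobile app after postintervention measurements".
- **Expected events** (Safety): autonomic dysreflexia, pressure ulcers and shoulder pain, because these "can occur because of physical strain or are common complications after SCI".
- **Reporting** (Safety): "Participants will be instructed to report any AEs or health-related interruption of the intervention within 24 hours".
- **Numbers** (Study Design, Randomization, Sample Size): 30 participants at the sport university are randomised 1:1. A further 15 at the clinic in Tübingen are not randomised and contribute to the primary outcomes.

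**The concern.** A concurrent control group helps a safety assessment by showing how often events occur without the intervention. That matters here, because the plan itself describes the expected events as common after spinal cord injury. If only related events are counted, this background is removed from the control arm before the comparison is made. It is not fully removed from the app arm, where shoulder pain, for example, can plausibly be attributed to the exercises.

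The comparison can then mislead in either direction. An excess in the app arm may be a product of the definition. A control count made up of events from test visits may look like a benchmark without being one for six weeks of home exercise.

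The sentence also compares a number of events. That is harmless with equal groups, but not if the intervention group is about twice as large as the control group.

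**Working it through.** The plan gives no AE rate, safety threshold or power for this outcome, so there is no figure of its own to reproduce. The inputs taken from it are the group sizes: 30 + 15 = 45 in total, and 30 at 1:1 gives 15 versus 15. All event rates below are assumptions, shown over a range.

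**1. What the control count can contain**

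| Reading of *study-related* | App arm | Waitlist arm |
|---|---|---|
| Same as *intervention-related* | events attributed to the app programme | zero by definition, as there is no app until after t1 |
| Caused by any study procedure | app programme plus test procedures | essentially the ramp and handgrip tests at the sport university |

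Under neither reading does the waitlist count estimate the background rate during the six weeks.

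**2. What a definitional zero does**

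Assume the same background risk p per participant in both arms, no true effect of the app, and a share q of app-arm events attributed to the app. The expected number of related events among 15 app users is 15pq, against 0 in controls. The chance of at least one apparent excess event is 1 − (1 − pq)^15.

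- p = 0.2, q = 0.5: 15 × 0.2 × 0.5 = 1.5 events expected against 0, and 1 − 0.9^15 = 79%.
- Over p from 0.1 to 0.3 and q from 0.25 to 0.5, the chance runs from 32% to 91%.

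The plan names no test. For scale only, 5 of 15 app users with an event against 0 of 15 gives a two-sided Fisher p of 0.042, although that zero carries no information.

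**3. Raw numbers with unequal groups**

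Assume all-cause events are Poisson with the same rate r per person over six weeks in both groups. The table gives P(app count > control count), with control mean 15r and app mean 15r or 30r.

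| r | 15 vs 15 | 30 vs 15 |
|---|---|---|
| 0.1 | 38% | 68% |
| 0.2 | 42% | 80% |
| 0.5 | 45% | 93% |

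At r = 0.2 the expected counts are 3 versus 3, or 6 versus 3. The 30-versus-15 column applies only if all 15 clinic participants use the app and are counted in the intervention group. It models all-cause events, so it shows the effect of omitting the denominator and not the effect of the relatedness filter.

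**4. What the proposed analysis can deliver**

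At 15 versus 15, with an all-cause comparison of participants with at least one event, Fisher power is 4% for 20% versus 10%, 15% for 30% versus 10%, and 25% for 50% versus 20%. For related events in app users, zero observed gives an exact two-sided 95% upper limit of 1 − 0.025^(1/n): 21.8% for n = 15 and 11.6% for n = 30.

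**The case against.** **The two terms differ.** A reader might infer that controls cannot have any countable event. The document does not support that. Controls at the sport university undergo a ramp test to exertion and maximal grip testing, so they can have study-related events. This stands: the control count is not necessarily zero. But events from testing do not measure background during the home programme, so the comparison still fails its purpose.

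**The outcome survives without the comparison.** A reader might infer that the primary safety outcome is uninterpretable. It is not. The Safety section defines it by the occurrence of related events, graded for severity and expectedness, and the interviews cover perceived safety. All of this can be read in app users alone. This also stands, and it confines the defect to the between-group sentence.

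**The 30-versus-15 split is not stated.** The flowchart is not shown, and the Study Design section describes the intervention group as formed after randomisation. The interim 8 versus 4 in Table 3 fits a larger intervention group but does not establish it. The 80% figure is therefore conditional.

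**Reporting already covers both arms.** A reader might infer that controls are told to report less. The instruction is addressed to participants generally and covers any AE. Reference to interruption of the intervention and a post-intervention interview for app users only may prompt them more, but a difference in reporting is conjecture.

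**Detail may sit elsewhere.** Denominators and intervals are often left to a fuller document, and their absence alone would not be a finding. What is at issue is the event definition and the comparison that the article does fix. The limits that small numbers impose are conceded under Strengths and Limitations.

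**Conclusion.** The point holds for the between-group comparison. The Safety and Quantitative Analysis sections use two different, undefined relatedness terms. Under either reading, the waitlist count cannot show whether the programme raises AEs above background. This follows from the text and needs no assumed rate.

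The size of the distortion does rest on assumptions. With no true effect, the chance of at least one apparent excess event against a definitional zero is 79% at a background risk of 20% with half of app-arm events attributed to the app (range 32% to 91%). If the intervention group is about 30 and the controls 15, raw all-cause counts at equal rates favour the controls in 80% of trials at 0.2 events per person, against 42% with equal groups.

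The descriptive assessment of related events in app users is unaffected.

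**What to change.** 1. Choose and define one relatedness term, and use it in both the Safety and Quantitative Analysis sections.
2. Between arms, compare all AEs and SAEs regardless of relatedness, among the 30 randomised participants only. Report participants with at least one event and events per person-time, with exact 95% confidence intervals.
3. For all app users, report intervention-related AEs and SAEs by severity, descriptively, with an exact 95% confidence interval. State the upper limit in any conclusion on safety.
4. Collect AEs in the same way in both arms, for example with the same fixed question at t1 and in the diary. The Feasibility section already says "participants in both the intervention and waitlist control groups will be provided with an exercise diary". The diary form is not shown, so whether it has room for such a question needs checking.

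**Cost.** The change is to analysis wording and one common question. It needs no extra participants or visits, and participants are already told to report any AE. More minor events will be recorded. At about 15 versus 15 the all-cause comparison is fair but imprecise, so it should be read through its confidence interval, and a lack of difference should not be taken as evidence of safety.

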### Ethics Approval

The conduct of the trial was approved by the ethics committee of the GSU (ethics committee number 180/2021). Comprehensive study information is sent to potential study participants before their first site visit to allow sufficient time to fully read and understand all the information. Study information includes details on the following: (1) general information and background; (2) eligibility criteria; (3) study aims and procedures; (4) participants’ rights, duties, and benefits; (5) potential risks; (6) data protection and management; (7) insurance; (8) funding; and (9) contact persons.

Participants will confirm that they have read, understood, and agreed to the terms of study participation by providing written informed consent before inclusion in the trial.

Precautions that will be taken to minimize the risk of cardiovascular events and AEs include the application of exclusion criteria, the conduct of a medical screening before enrollment, the distribution of a safety advice sheet, and integration of safety advice into the app.

To ensure confidentiality, we pseudonymized all participants’ data (refer to the *Data Management* section). Participants will receive compensation for travel expenses and the interpretation of their test results upon study completion. Any amendments to the protocol will be documented, and substantial changes will need to be approved by the ethics committee.

## Results

This trial is part of the FIT-IN^3^ (ParaGym) project, which is funded by the German Federal Ministry of Education and Research in September 2020 (funding number 16SV8572). The project started in September 2020 and is expected to be completed by August 2023. Recruitment for the trial began on November 1, 2022. A total of 12 participants were enrolled in the trial at the time of the submission of this manuscript (Table 3). Data collection will begin in January 2023 and is expected to be completed by April 2023. The results will be published in accordance with the CONSORT (Consolidated Standards of Reporting Trials) 2010 statement for randomized pilot and feasibility trials [69] as well as the CONSORT-EHEALTH (Consolidated Standards of Reporting Trials of Electronic and Mobile Health Applications and Online Telehealth) statement [70].

**Table 3 table3:** Characteristics of the participants (n=12) enrolled in the study at the time of submission.

Characteristics			Intervention group (n=8)		Control group (n=4)
**Gender, n (%)**					
	Women	4 (50)		2 (50)	
	Men	4 (50)		2 (50)	
Age (years), median (IQR)			55 (37-62.5)		34 (18.5-56)
**Lesion level, n (%)**					
	T1-T6^a^	3 (38)		0 (0)	
	T7-S5^b^	5 (62)		4 (100)	
**Lesion completeness, n (%)**					
	Motor complete (AIS^c^ A-B)	6 (75)		2 (50)	
	Motor incomplete (AIS C-D)	2 (25)		2 (50)	
Time since injury (years), median (IQR)			11 (4.5-26.5)		17 (8-24.5)
**Experience with exercise apps, n (%)**					
	Yes	4 (50)		0 (0)	
	No	4 (50)		4 (100)	

^a^T: thoracic vertebra.

^b^S: sacral vertebra.

^c^AIS: American Spinal Injury Association Impairment Scale.

## Discussion

### Principal Findings

To the best of our knowledge, this is the first trial to investigate the feasibility, usability, and safety of a 6-week exercise program delivered by an intelligent mobile exercise app for individuals with paraplegia using qualitative and quantitative measures. As secondary outcomes, the preliminary effects of this program on peak exercise capacity, handgrip strength, independence, and quality of life will be assessed. As the app is currently at a prototype stage, technical issues compromising feasibility and usability might occur. Both the semistructured interviews and exercise diaries will provide detailed insights into the users’ experience with the app. This will help identify various aspects regarding the feasibility and usability of the exercise sessions, app’s interface, and app’s technical functionality, including intelligent personalization. Furthermore, users’ practical suggestions for improvement will contribute to drawing practical implications. These could include the following: (1) further adapting the app to meet the needs of the target group; (2) fixing technical issues; (3) improving the ease of use, (4) improving the design, intensity, and duration of the exercise sessions; and (5) improving the overall satisfaction with the app. Before integrating the exercises into the app, all exercises, including the exercise videos and descriptions, were tested and evaluated in terms of feasibility, usability, and comprehensibility by 10 workshop participants with paraplegia. Therefore, we expect these exercises to be feasible and usable. The program is expected to be safe, as a very low incidence of AEs has been reported during exercise trials with this cohort [49,71].

Similar mobile apps for promoting a healthy lifestyle in people with SCI have been shown to be feasible [27,28]. However, these apps were not declared to be at a prototype stage. In contrast to these already existing mobile apps, the ParaGym mobile exercise app delivers individualized training sessions without the need for exercise selection by the users or health care professionals. Thus, training sessions can be performed independently by people without specific knowledge of training and exercise. In fact, the most frequently mentioned suggestion for improvement of the WHEELS app [27] was related to personalization and better tailoring to the user’s needs and functional capabilities.

This trial will provide preliminary insights into the potential effects of the intervention on peak exercise capacity, handgrip strength, independence, and quality of life. Integrated exercises were designed to be appropriate for a beginner’s fitness level, so they will be feasible for most participants.

### Strengths and Limitations

Using the SPIRIT 13 Guidelines [31,72] for reporting the planned trial and the SCI trial guidelines [51,73] for designing as well as randomizing and controlling the trial improves its strength. In addition, the GSU cooperates with the BG clinic Tübingen to reach a larger sample size. Another strength is the compatibility of the app with various operating systems such as iOS (Apple Inc) and Android. However, smartphones should not be older than approximately 5 years to guarantee absolute functionality.

The ParaGym mobile app is currently at a prototype stage. Therefore, only basic functions and features are currently included. This could impact the variety of exercises, especially for users with severe impairments, which may decrease their motivation to use the app. The conclusiveness and generalizability of the results will be limited owing to the small sample size. In addition, only healthy adults with paraplegia were included in the study. Therefore, many individuals will be excluded from the study. Generalizability is also limited because the prevalence of cardiovascular diseases is high in individuals with SCI [74,75]. In addition, not restricting additional sports activities may have a major impact on the postintervention measurement results. Moreover, selecting exercises that are mainly suitable for beginners may compromise the effectiveness for intermediate users. Finally, all exercises will be performed using body weight or a resistance band, which will limit the user’s opportunity to increase intensity compared with using additional weights.

### Conclusions and Implications

By using both qualitative and quantitative measures, the results of this trial will generate a comprehensive understanding of the limitations and strengths of the ParaGym mobile exercise app as well as possible solutions to address the limitations. In the next step, in addition to fixing technical issues, the app should be adapted according to the findings of this study. This could include the expansion of the exercise pool and the addition of more equipment to increase variability and meet the needs of more advanced users. Hence, this could lead to an increased intensity of exercise sessions, which might result in greater effectiveness. Furthermore, the app interface might need to be adjusted to improve the ease of use. Finally, users may desire more features, such as the opportunity to design individual workouts or the integration of gamification to visualize the training process and promote adherence.

This pilot study will provide important results that need to be considered in the planning of future trials with an updated version of the app, which would aim for a larger sample size, longer intervention duration, and more diverse target group. As other individuals who use wheelchairs may also benefit from using the app, a requirement analysis addressing a broader target group should be conducted. Subsequently, a full-scale multicenter trial [73] including a broader target group, for example, people with acute SCI, tetraplegia, or other impairments, should be undertaken. In addition, by solely including healthy adults with SCI, a large proportion of the population was excluded. The prevalence of secondary diseases, such as cardiovascular diseases, is higher in individuals with SCI than in able-bodied people [74,75]. Therefore, investigators of future trials should consider including individuals with secondary diseases to assess the safety of the intervention for this group as well. Finally, future trials should include follow-up measures to investigate long-term motivation and adherence. In the long term, a fully marketable version of the ParaGym app should be implemented to make it publicly accessible.

An additional application of the ParaGym app could be its incorporation into workplace health programs, offering an exercise program for individuals who use wheelchairs and individuals with high levels of sedentary time at work.

A feasible, usable, and safe intelligent exercise app would increase access to personalized, independent, and evidence-based exercise training for this cohort and, in the future, for other individuals who use wheelchairs.

